#### Sample

The goal for Aim 2 is to recruit 24 adults; 12 individuals in the mobile and technology-assisted aftercare group and 12 individuals in the standard services group. These adults will be recruited equally across the three participating jurisdictions resulting in eight participants per county. Individuals brought to the CSU by law enforcement will be randomly assigned to one of two study conditions in equal proportions. To be eligible for participation in Aim 2, individuals must be age 18 or older, English speaking, will discharge to one of three participating counties and plan to remain in the county for 6 months, admitted to the CSU through law enforcement, consent, and the cognitive capacity to understand study participation and to consent. This sample size is strategically small due to testing the feasibility of accessing the needed sample size for future studies. With this pilot sample size, we will be looking at the feasibility of recruiting individuals in a vulnerable, highly transient, population, and retention trends. Both feasibility of recruitment and retention trends will impact our decision on a larger sample size in the subsequent RCT.

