#### Randomization

In Aim 2, participants who will be recruited from the CSU will be randomized into either the control group (treatment as usual) or the intervention group (technology-assisted mobile aftercare) by the research team. Due to the short length of stay in a CSU, the research team will use a one-to-one randomization procedure and pre-randomize the pool of participants prior to recruitment. To do so, the research team will create an allocation table with the total participant slots (*n*=24) and then use a random sequence generator to pre-randomize each slot as either the control group or the intervention group. The randomized allocation table will be uploaded into our online database where the randomization status will only be visible to the research team member upon completing the consent process with a participant. Following these guidelines eliminates the potential for human error or bias into who receives the mobile aftercare intervention. Participants will be notified of their randomization status at the end of the consent and baseline data collection interview by the research team. It is necessary to inform the participants of their randomization group because the interventionist will contact participants in the treatment group within 24 hours to set up their first appointment.

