#### Measures

Measures for the Mobile and Technology-Assisted Aftercare Group and Standard Services Group include administrative records and direct data collection from participants. The primary outcomes for this feasibility study are participant recruitment, participant retention, feasibility, and the acceptability of the intervention. Participant recruitment will be measured by the number of eligible participants who consent to participate out of the total number of eligible participants. Participant retention will be measured by the proportion of the intervention completed by participants. Feasibility and accessibility will be assessed by triangulating the qualitative and quantitative data from study participants—the CSU professionals and patients.

 The secondary outcomes include individual stabilization and well-being, frequency of both acute and long-term treatment use, re-admission to a crisis stabilization unit, and arrest rates or re-encounters with law enforcement. The secondary outcomes will be assessed to find trends that will inform the future RCT. We will examine the feasibility of collecting the data, the sensitivity of the measures, estimates for effect size and sample size, and other factors that may impact the ability to detect outcomes. For the pilot study, the secondary outcomes are not meant to measure impact; instead, they are intended to examine trends in outcomes to inform the design of the intervention and study protocol for the future RCT. Secondary outcomes will be measured using screening questions, demographical information, clinical assessment tools, and baseline and follow-up interviews with each participant. Administrative data from the CSUs and law enforcement will be collected on client characteristics, including demographics (e.g., race, gender, age, county of residence), criminal history (e.g., current reason for law enforcement contact, prior arrests, and reasons for arrest, and prior CSU stays), and behavioral health status (e.g., diagnoses, prior and current treatment utilization, and medication-assisted treatment). Table 3 shows the measures related to each secondary outcome described below.

**Table 3 Tab3:** Primary and secondary measures

**Primary outcomes**	**Measures**
Participant retention	Number of recruited participants who complete the intervention
Participant recruitment	Number of eligible participants who agree to participate out of the total number of eligible participants

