#### Data collection

Data collection with recruited participants in the treatment and control groups will occur approximately four times throughout participation. The baseline interview will be conducted immediately following enrollment and consent before the participant discharges from the CSU. The remaining three data collection points include the complete data collection toolset. The first data collection sessions (T1) will occur 2 weeks post-discharge from the CSU. The second data collection point (T2) will be 3 months post-discharge from the CSU. Lastly, the third data collection session with recruited participants will occur 6 months post-discharge from the CSU (T3). These data collection sessions will be conducted at the participant’s home or a nearby public location that the participant requests.

Data from recruited participants will be collected using validated assessment tools, qualitative surveys, and administrative data. These data collection methods will be consistent throughout T1–T3 sessions for the mobile and technology-assisted group and the standard services group. However, the qualitative CSU experience survey may vary based on the participant’s situation. Specifically, the CSU experience survey will be collected only at the T1 interview unless a participant is readmitted to the CSU. If a participant is readmitted to the CSU, the CSU experience survey will be re-asked at the data collection interview following the CSU admission.

Administrative data will be collected for 6 months following enrollment. Additional administrative data will be collected from law enforcement agencies to identify arrests and police contact of participants. Although we will not be assessing for causality in the current proposal, it is critical for us to pilot the collection of these data as they are integral to the follow-up multi-site RCT.

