#### Analysis strategy

Data collected from the Mobile and Technology-Assisted Aftercare and Standard Services Groups will allow researchers to gather preliminary data comparing those that receive standard CSU services to those that receive CSU services plus the mobile and technology-assisted aftercare support. Patterns will be monitored to assess the primary and secondary outcomes listed in Table 3. A mixed-data analysis plan, including descriptive statistics (means, proportions, frequencies, and percentages) and bivariate analyses, will be used to capture the range of qualitative and quantitative data present in this study’s primary and secondary outcomes. The study is not designed to detect differences in clinical outcomes; thus, the focus of the analysis provides preliminary information on trends in outcomes and some potential underlying contributors to those trends. These data will provide essential information for advancing knowledge of CSUs and information necessary to inform the future RCT. Qualitative data related to the primary outcomes will be analyzed using the approach described in the Aim 1 analysis strategy. Quantitative analysis for primary outcomes will be conducted using a comparative analysis both within groups and across time. The bivariate analysis will be used to assess correlations and regressions. Additionally, preliminary ANOVAs will be used to assess the trends of participants. Qualitative and quantitative data will be combined using a sequential mixed methods design. Equal weight will be given to the qualitative and quantitative data sources. Data will be reviewed and analyzed for any significant variations that can help assess trends in participants over time and across groups through mean comparison tests.

Mixed methods analysis will be used to assess both primary and secondary outcomes. We will integrate the findings from each of the quantitative and qualitative components [56] by conducting comparative analyses both within and across groups, over time, so that we may examine differences at the county level in terms of quality and fidelity of the intervention. Data will be integrated with quantitative outcome measures, fidelity data, and qualitative interviews using a sequential mixed methods design with equal weight given to qualitative and quantitative data sources [56, 57]. Data will be assessed for significant variations, and qualitative data is used to help us understand quantitative data trends when warranted.

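### The arm comparisons of the secondary outcomes name no baseline adjustment, although matching pre-enrolment values are collected; adding it is a cheap, low-priority gain in precision

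*Protocol article*

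**What the plan says.** The Aim 2 Analysis strategy states its quantitative methods for the primary and secondary outcomes. It lists "descriptive statistics (means, proportions, frequencies, and percentages) and bivariate analyses", adds that "The bivariate analysis will be used to assess correlations and regressions", mentions preliminary ANOVAs, and closes by saying that the data will be used to "assess trends in participants over time and across groups through mean comparison tests". No covariate and no baseline adjustment is named.

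The Measures section of Aim 2 says that administrative data will cover "criminal history (e.g., current reason for law enforcement contact, prior arrests, and reasons for arrest, and prior CSU stays", and also prior and current treatment utilization. These items are counterparts of three secondary outcomes in Table 3: arrests, CSU re-admission and treatment use. The Data collection section adds that "The baseline interview will be conducted immediately following enrollment and consent before the participant discharges from the CSU". It states the full toolset only for the three later sessions (T1 to T3).

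The Sample section plans "12 individuals in the mobile and technology-assisted aftercare group and 12 individuals in the standard services group". The Randomization section will "use a random sequence generator to pre-randomize each slot as either the control group or the intervention group" and describes no stratification on history.

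On use, the Measures section says that the secondary outcomes are not intended to measure impact, but that they will serve "estimates for effect size and sample size". The Aim 3 section makes the first progression criterion whether the pilot results point to positive effects in the treatment group.

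**The concern.** With 12 people per arm, the arms can differ by chance in prior arrests, prior CSU stays or prior treatment use. If history predicts what follows, the arm that starts worse will tend to end worse whatever the aftercare does. A plain comparison of means then reports part of that starting difference as a trend. The plan uses these trends twice: as effect-size and sample-size inputs for the future RCT, and as evidence for the first progression criterion. The values needed to remove part of this noise are already being collected.

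The primary outcomes (recruitment, retention, feasibility, acceptability) have no baseline counterpart and are not affected.

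**Working it through.** **Inputs.** From the article: 12 per arm, allocated 1:1. The article gives no SD, target effect, alpha, power, dropout rate or baseline-outcome correlation (rho), so it has no figure of its own to reproduce here. Assumptions: outcomes in SD units, normally distributed, no dropout, and rho of 0.3, 0.5 or 0.7.

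**Chance imbalance.** The SE of a standardized baseline difference is √(2/12) = 0.408 SD. The chance of an absolute difference of at least 0.5 SD is 2 × [1 − Φ(0.5/0.408)] = 0.22. For a yes/no history item, the exact binomial chance that the arms differ by 3 or more of 12 is 20%, 28% or 31% at a prevalence of 20%, 33% or 50%.

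**Carry-over to the outcome.** A baseline imbalance of 0.5 SD shifts the unadjusted arm difference by 0.5 × rho = 0.15, 0.25 or 0.35 SD.

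**Precision with one covariate.** The adjusted SE is 0.408 × √(1 − rho²) × √(21/20), where the last factor is the small-sample cost of estimating the slope. The 95% half-width uses t with 22 degrees of freedom unadjusted and 21 adjusted. The change-score SE is 0.408 × √(2(1 − rho)). The equivalent unadjusted size per arm is 12 / [(1 − rho²) × 1.05].

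| rho | Unadjusted SE | Adjusted SE | Change-score SE | 95% half-width, unadjusted → adjusted | Equivalent n per arm |
|---|---|---|---|---|---|
| 0.3 | 0.408 | 0.399 | 0.483 | 0.85 → 0.83 | 12.6 |
| 0.5 | 0.408 | 0.362 | 0.408 | 0.85 → 0.75 | 15.2 |
| 0.7 | 0.408 | 0.299 | 0.316 | 0.85 → 0.62 | 22.4 |

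A simulation of 20,000 trials per rho agreed with the unadjusted and adjusted SEs. Both estimators averaged zero under no effect, so neither is biased.

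**Cost if the covariate is useless.** At rho = 0 the SE is multiplied by √(21/20) = 1.025, so it is about 2.5% larger.

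**Effect on the direction of a trend.** For a true effect of 0.5 SD, the chance that the estimate has the wrong sign is Φ(−0.5/SE): 11.0% unadjusted, and 10.5%, 8.4% or 4.7% adjusted. With no true effect, the simulated chance of an apparent benefit above 0.3 SD is about 23% unadjusted, and 23%, 20% or 16% adjusted.

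**The case against.** **The article never calls the comparisons unadjusted.** A reader might infer that adjustment is ruled out. It is not: regressions and ANOVAs are mentioned, and model terms could sit in an analysis plan not shown here. What stands is narrower. The methods that are named are bivariate analyses, ANOVAs and mean comparisons, with regression placed under the bivariate heading, and a better use of data already collected can be set against them.

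**Bias.** A reader might infer that the planned contrast is biased. Randomization keeps it unbiased on average, and its SE already allows for chance imbalance. The loss is precision.

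**Design inputs.** A reader might infer that the pilot cannot give the RCT a baseline-outcome correlation or a residual SD. The planned correlations could supply the first, and with the total SD the second follows. The text simply does not name them as outputs.

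**Over-time analysis.** An ANOVA that includes baseline could absorb some imbalance. At rho 0.7 a change-score contrast comes close to the adjusted one (0.316 against 0.299). At 0.5 it gains nothing over the unadjusted contrast, and at 0.3 it is worse. The article does not say whether baseline enters the ANOVA.

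**Counts and scales.** The precision figures assume normal outcomes. Arrests and re-admissions in 12 people per arm may be sparse counts, and the figures do not carry over to them. Scale scores may be missing at baseline. Both objections stand and limit the remedy.

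**Purpose.** The study disclaims any test of clinical differences, so power is beside the point. That lowers the priority, but the arm trends still feed the sample-size estimates and one of four progression criteria.

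**Conclusion.** The point holds as a free or cheap improvement of low priority. The named methods leave avoidable noise in the arm trends, and matching pre-enrolment values are collected for arrests, CSU re-admission and treatment use. The gain depends on a correlation that the article does not give: negligible at 0.3, about three extra participants per arm at 0.5 (15.2 against 12), and substantial at 0.7. These sizes assume normal outcomes and no dropout.

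Even at 0.5 the adjusted 95% half-width is 0.75 SD. Adjustment would not make the pilot's effect estimate a secure basis for sizing the RCT or for the first progression criterion, and the documents do not support describing the planned comparison as invalid.

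**What to change.** Add one paragraph to the Aim 2 Analysis strategy:

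- For each quantitative secondary outcome that has its own pre-enrolment value, keep the unadjusted summary. Beside it, report an arm difference adjusted for that single value, with a 95% CI, the residual SD and the baseline-outcome correlation as design inputs for the RCT.
- Use a scale's baseline score only where that scale was actually given at the baseline interview. Do not use T1 as a baseline, because it comes two weeks after discharge and follows the start of the intervention.
- For arrests and re-admissions, fit a count model adjusted for prior arrests or prior CSU stays only if events are frequent enough for stable estimates. Otherwise describe the outcome by arm next to the prior-history values.
- Keep the descriptive summary for outcomes without a pre-enrolment value.

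This needs no new data, visits or staff. For continuous outcomes the cost is one degree of freedom per model, with an SE about 2.5% larger if the correlation is zero.

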### Aim 3 study design

#### Aim 3: Design a multi-site RCT to compare the relative impact of CSUs with mobile and technology-assisted aftercare to CSUs without mobile and technology-assisted aftercare

The goal of Aim 3 is to design a large-scale multi-site RCT to compare CSUs with and without mobile technology-assisted aftercare on short and long-term outcomes. It is anticipated that the outcomes in this future RCT will include individual stabilization post-crisis, arrest rates, use of acute services, and increased engagement with long-term treatment

To reach Aim 3, the qualitative data from CSU stakeholders in Aim 1, and data from the pilot trial of the CSU aftercare intervention in Aim 2, will be synthesized to inform and develop a study protocol for the future large-scale RCT. Following the guidelines from the CONSORT extension to pilot trials, data from Aims 1 and 2 will be used to inform the feasibility and suggest critical areas where further development or modification may be required [58]. For instance, data from Aim 1 will explore barriers and facilitators to intervention implementation for agencies and the perceived acceptability of the intervention for our target population and stakeholder procedures. Analysis of Aim 2 data will inform sample size details, referral, appropriate randomization procedures, retention and attrition challenges, and whether randomizing to follow-up mobile supports is the correct variable to randomize on or if there is another more appropriate randomizing variable. Prespecified progression criteria will be assessed from our pilot study to determine whether to proceed with the development of the future RCT. Our progression criteria include the following: (1) do the results of the pilot study suggest positive effects on the treatment group?; (2) did feedback from participants and stakeholders demonstrate the feasibility and acceptability of the intervention?; (3) can a future RCT feasibly be implemented?; and (4) are there potential future partners for a future RCT?

Recommendations to avoid common mistakes during small-scale pilot trials like this one include capturing data on acceptability and feasibility and information on secondary outcomes [59]. Our data on participant outcome trends directly responds to this recommendation. Outcome trends observed in participants will include the use of acute services, engagement with long-term treatment, arrest rates, and multiple factors of individual stabilization (i.e., financial stability, employment stability, perceived social support, and psychological well-being). Ultimately, this data will provide a greater understanding of our target population, including common challenges and experiences with the intervention. This process enables careful refining of the intervention for Aim 3 before a large-scale RCT.

## Study timeline

This study will take approximately 2 years to complete. The estimated time necessary to complete each of the three aims is detailed in Table 4. This study does not operate on a strict linear timeline, and the data collection and analysis of Aims 1 and 2 may overlap or occur coincidingly. However, Aim 3 will not begin until Aims 1 and 2 have been completed.

**Table 4 Tab4:** Study timeline

**Study timeline**	2 mths	4	6	8	10	12	14	16	18	20	22	24
**Aim 1**												
Research preparation and stakeholder establishment	x											
Qualitative interviews w/ CSU stakeholders and iterative analysis		x	x	x	x	x	x	x	x	x		
**Aim 2**												
Pilot test activities				x	x	x	x	x				
Data analysis and implementation guide								x	x	x		
**Aim 3**												
Study protocol development and completion										x	x	x

## Discussion

Because short-term crisis centers, like CSUs, are increasingly being implemented in communities, it is critical to understand how these facilities operate as a jail alternative for law enforcement who have frequent contact with persons experiencing a behavioral health crisis [11, 12]. Similarly, research must discern CSU processes and how community care systems may minimize subsequent contacts with law enforcement and re-admission into CSUs for CSU patients. This study responds to this need by initiating a feasibility study examining critical CSU implementation and adoption elements while piloting an aftercare program for persons brought to the CSU by choice of law enforcement.

Conducting and exploring the feasibility and acceptability of CSU aftercare services is a critical first step in identifying how to implement CSUs as alternatives to arrest realistically and most effectively in diverse jurisdictions across the country. This study enhances our feasibility and acceptability data by engaging perspectives from a variety of stakeholders involved in CSU processes, including law enforcement, behavioral health staff, and CSU patients. Feasibility and acceptability data will come from a combination of qualitative interviews and quantitative analysis of the deployment of intervention-specific techniques and outcomes trends.

This study comes at a crucial moment in time as policymakers seek police reforms and alternative responses to issues that are more closely related to public health rather than public safety. Results from this study will advance the identification and dissemination of evidence-driven CSUs and yield three important products: (1) feasibility evaluation results that address jurisdictional variation and establish important feasibility guidance for practitioners and policymakers, (2) an implementation guide for future refinement and adopters of CSUs initially to be used to pilot test the CSU with follow-up mobile and technology-assisted aftercare, and (3) study protocol design for a future large-scale RCT of CSUs with follow-up mobile and technology-assisted aftercare. If mobile and technology-assisted aftercare pilot intervention demonstrates significant feasibility and acceptability, we are prepared to develop a large-scale RCT. An expansive RCT will further the evaluation of CSUs and enable a more generalizable analysis of CSU aftercare services on the persons who are a recipient of them. Understanding the effects of CSU aftercare services on persons may guide policy and national understanding of effective criminal justice diversion for persons with behavioral health disorders.

